### Analytic Plan

1-way repeated measures Analysis Of Variance (RM-ANOVA) will be used to evaluate test-data within groups for assessments at baseline, 9 and 21 weeks. 2-way ANOVA (group × time) will be used to test the effect of HIPRT for TC patients (STR vs. UNT), and BEP-treatment for training response (STR vs. CON) respectively. The equivalent non-parametric tests will be used for mRNA expression and protein levels. Significance level of 0.05 is chosen.

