### Study Endpoints and Assessment

During the course of the study the participants will carry out physical tests, have invasive biological samples taken and complete standardized questionnaires. The schedule for individual data assessment is presented in table 2, and the study endpoints are summarized in table 3.

**Table 2 T2:** Data Assessment Schedule

Data assessment	Baseline test Day - 5-0	Treatment start Day 1	2^nd ^cycle start Day 22	3^rd ^cycle start Day 43	Post interv. test Day 64-66	Follow-up test ~ Day 150
Muscle biopsy	x				x	x
Blood sample	x		x	x	x	x
DXA scan	x				x	x
Strength test	x				x	x
Questionnaires (SF 36 & EORTC)	x		x	x	x	x
Randomization		x				

**Table 3 T3:** Study Endpoints

Muscular morphology
• Mean fiber area
• Fiber type distribution
• Satellite cells
• Intracellular signaling molecules
Body Composition
• Lean Body Mass
• Fat percentage

Muscle strength
• Maximum Voluntary Contraction
• Leg Extensor Power

Systemic effects
• Cholesterol (TCHO, HDL, LDL, Triglycerides)
• Glucose
• Insulin
• Inflammatory markers (CRP, TNF-α, IL-6, IL-18)
• Anti-inflammatory markers (IL-4, IL-10)

Patient reported outcomes
• Health related Quality of Life (SF-36 and EORTC)

The healthy control subjects will carry out the same testing protocol and have the same biological samples taken, but will not receive cancer specific questionnaires.

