### Sample size

Sample size is chosen to ensure significant muscular hypertrophy, evaluated by mean fiber area, in CON, among whom a 15% increase is estimated according to earlier studies.

N > (1,28*√(0.15*0.85))^2^/(0.15^2^) = 9,28. A minimum of 10 is required in each group, but due to clinical experience concerning possible drop out due to medical reasons 15 are included in each group.

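### RM-ANOVA over three visits discards week-9 data from men who lack only week 21, although the plan itself provides for medical dropout

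*Protocol article*

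**What the plan says.** Two analyses are fixed in the Analytic Plan. Within groups, "1-way repeated measures Analysis Of Variance (RM-ANOVA) will be used to evaluate test-data within groups for assessments at baseline, 9 and 21 weeks". Between groups, "2-way ANOVA (group × time) will be used to test the effect of HIPRT for TC patients (STR vs. UNT"), with a parallel comparison of STR with CON. The label of repeated measures is attached to the first only, and the visits are named for the first only.

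The Sample size section concludes from its formula: "A minimum of 10 is required in each group". Enrolment is then set higher, and the reason offered for the extra five is this: "due to clinical experience concerning possible drop out due to medical reasons 15 are included in each group". No dropout rate is given.

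Table 2 schedules the muscle biopsy, DXA scan and strength test three times: at baseline, at Day 64-66 and at about Day 150. STR and UNT are managed differently only up to the second of these. After chemotherapy, both are offered a 12-week rehabilitation program (study arms 1 and 2).

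**The concern.** The plan makes room for men leaving for medical reasons and then names a method that, as usually run, cannot use a man with a missing visit. The trial's contrast between training and usual care ends at week 9, yet whether a man's week-9 biopsy counts would depend on whether he returns for a third biopsy about 12 weeks later.

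Two things are at stake. The first is precision: data already collected from small groups are thrown away. The second is bias. The stated reason for loss is medical, and the Discussion expects nausea, febrile neutropenia and infections to interfere with training. If the men worst affected by treatment are the ones who leave, completers will show less muscle loss than the whole group, and the effect of BEP on muscle is part of the primary aim.

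The wording of the 2-way test raises a related difficulty. If it were run as an ordinary factorial ANOVA, the repeated values from one man would be treated as independent.

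**Working it through.** **1. The plan's own figures.** The printed formula is "N > (1,28*√(0.15*0.85))^2^/(0.15^2^) = 9,28". Computed: 1.28² × 0.15 × 0.85 / 0.15² = 9.284, rounded up to 10. Going from 10 to 15 implies a loss of 1 − 10/15 = 33.3%, and 10/(1 − 1/3) = 15. The figures agree with one another, but the one third is inferred. (Whether this formula suits mean fiber area is a separate question.)

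**2. Who remains, if one third of 15 are lost in total.**

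| When the losses occur | With week-9 data | Complete at all three visits |
|---|---|---|
| All before week 9 | 10 | 10 |
| Half before, half after | 12.5 | 10 |
| All after week 9 | 15 | 10 |

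RM-ANOVA uses the last column. What it wastes is the gap between the columns: none in the first row, 5 men per group in the third.

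**3. Precision.** In the third row the standard error of a week-9 change or contrast rises by √(15/10) = 1.225, or 22%. As an illustration, take a baseline-adjusted comparison of two arms, a true difference of 0.9 SD and a correlation of 0.5 between visits (both assumed). Simulated power is then about 77% with 15 per arm and 57 to 59% with 10.

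**4. Bias within a group.** Assumptions not in the protocol: SD of the week-9 change in fiber area 15 percentage points; true change in UNT −10%; correlation r between toxicity and muscle loss of 0.3 to 0.7; the most toxic third lost. Removing the upper third of a normal variable lowers its mean by φ(0.431)/(2/3) = 0.364/0.667 = 0.545 SD. Completers therefore look better by r × 15 × 0.545 points:

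- r = 0.3: +2.5 points
- r = 0.5: +4.1 points
- r = 0.7: +5.7 points

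Simulation gave the same values. With all available week-9 data instead, the bias is zero if all losses come after week 9, +1.3 to +3.2 points if they split evenly, and unchanged at +2.5 to +5.7 if all come before week 9. If losses are completely at random, neither approach is biased.

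**5. Bias in STR vs UNT.** On the same assumptions, with a true difference of 15 points: none if both arms lose men in the same way; +1.8 to +4.3 points if STR loses one third and UNT one fifteenth, with both arms analysed as completers.

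**6. The 2-way ANOVA without a subject term.** Simulated with 15 per arm, three visits, correlation 0.5 and nominal 5%:

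| Quantity | No subject term | With subject term |
|---|---|---|
| Type I error, group × time | about 0.5% or less | about 5% |
| Power, group × time, 0.9 SD | about 32 to 33% | about 70% |

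The error term then contains the variation between men, which does not belong in a test of change, so the interaction test is strongly conservative.

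**The case against.** Several objections carry weight.

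- **The sentence that names three visits covers the within-group tests only.** The 2-way test has no visits stated, and a baseline-to-week-9 comparison is a natural reading because UNT is offered training afterwards. On that reading a missing week-21 biopsy removes nobody from STR vs UNT. This stands, so the effect on the between-group tests is conditional.
- **Loss of numbers was planned for.** About 10 completers is what the sample-size section aims at. True, but that does not justify discarding week-9 biopsies already in hand.
- **Group × time is common shorthand for a mixed-design ANOVA.** Probably so here. It would then be complete-case as well, so the first problem returns if all three visits are used.
- **Toxicity occurs mostly during chemotherapy, before week 9.** For those losses, keeping all available data does not remove the bias. This stands and limits what the fix can do.

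Some stronger readings are tempting but not supported. A reader might infer that the randomised comparison is certain to be biased by a known amount. That needs loss that differs by arm or relates differently to outcome, and the protocol gives neither the pattern nor its strength. A reader might also infer that a 2-way ANOVA without a subject term would produce false evidence of a training effect. In simulation its test of the group main effect is indeed too liberal (about 17 to 20% at correlations of 0.5 to 0.7), but the group × time term, which tests differential change, errs the other way. Finally, the absence of a stated analysis for the Day 22 and Day 43 samples, or of named non-parametric tests, is detail that an article commonly leaves to the full plan.

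**Conclusion.** The point holds in limited form and should be acted on. As written, the within-group analysis discards week-9 data from men who lack only week 21; the between-group analyses do the same if they use all three visits. This follows from the named method and needs no assumption beyond its classical use.

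The cost in precision is at most a 22% larger standard error under the implied one-third loss, reached only if all losses fall after week 9. The bias in the within-group BEP effect, 2.5 to 5.7 points on a true −10%, is illustrative: it rests on an assumed SD, correlation and selection pattern. For STR vs UNT the size of any bias cannot be fixed from the document. The interaction power of about 33% instead of 70% applies only if the 2-way test is run without a subject term, which is probably not intended but is not excluded by the wording.

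**What to change.** Replace both ANOVAs with one linear mixed model containing group, time, group × time and a within-subject covariance structure, with a small-sample correction to the degrees of freedom such as Kenward-Roger. Include every participant with any assessment, in the group to which he was allocated. Name the STR vs UNT contrast at week 9 from this model as the main comparison, and take the within-group changes and STR vs CON from the same model.

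Because the model does not by itself deal with toxicity-related loss before week 9, report the number, timing and reasons of losses by arm beside the result.

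If the ANOVAs are kept, state at least that the 2-way test is repeated-measures, which visits it uses, and that week-9 data are kept when week 21 is missing.

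The cost is revised wording and slightly more analysis work, with no new data. The price is reliance on a missing-at-random assumption, which should be stated.

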### Randomization

Following the baseline test, TC patients will be allocated to either, STRength training (STR, n = 15), receiving a 9-wks HIPRT-program during treatment, or UNTrained (UNT, n = 15), who will receive standard care. The randomization procedure used is a simple adaptive biased-coin randomization. The inclusion criteria (men, aged 18-45, same diagnosis/stage of disease and treatment protocol) secure comparable groups in terms of sex, age and disease profile at baseline, and therefore no stratification will be carried out. The healthy CONtrol subjects (CON, n = 15) will be allocated to HIPRT without randomization.

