We have chosen to investigate the effect of a structured HIPRT program initiated at day 1 of the treatment, to avoid a pre-intervention deterioration. Carrying out an exercise program during the course of a very toxic treatment obviously causes practical challenges due to side-effects like nausea or febrile neutropenia, which may lead to infections. Also TC patients are hospitalized for the first 5 days of each cycle where they receive treatment (chemotherapy and fluids) for 8 to 10 hours per day. This design however, allows us to investigate the direct effects of antineoplastic therapy on skeletal muscle. To minimize confounding factors it is important to eliminate the effect of the tumor itself as much as possible. For this purpose TC patients are optimal, as they have a very responsive tumor and most likely the disease has only minor influence after the first cycle. TC patients, however, may be affected by the presence of hypogonadism, which can significantly affect muscular adaptations to resistance exercise. Up to 50% of leydig cells are lost at unilateral orchiectomy [46], and subnormal levels of testosterone have been found in long term TC survivors [47,48]. In healthy subject it has been shown that suppression of testosterone attenuates the response to resistance training [49], however whether TC patients undergoing chemotherapy experience attenuated exercise response because of treatment induced hypogonadism is currently unknown.

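### The trained-patients versus healthy-controls comparison relies on a common-variance ANOVA; an unequal-variance analysis would protect the 5% level if completer numbers and response spread differ between the groups

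*Protocol article*

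**What the plan says.** The Analytic Plan of the protocol article states that a two-way group × time ANOVA "will be used to test the effect of HIPRT for TC patients (STR vs. UNT), and BEP-treatment for training response (STR vs. CON"). The same method thus serves both comparisons, the second of them to judge how chemotherapy alters the training response. It adds "Significance level of 0.05 is chosen". Only some laboratory outcomes leave this framework: "The equivalent non-parametric tests will be used for mRNA expression and protein levels". Mean fibre area, strength and DXA outcomes therefore stay with ANOVA.

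The Randomization section plans equal sizes, with "STRength training (STR, n = 15") on one side. On the other, "The healthy CONtrol subjects (CON, n = 15) will be allocated to HIPRT without randomization".

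The Sample size section derives a minimum of 10 per group and explains the increase: "due to clinical experience concerning possible drop out due to medical reasons 15 are included in each group". It gives no dropout rate by arm. The Discussion says of the patient arm: "Carrying out an exercise program during the course of a very toxic treatment obviously causes practical challenges", naming nausea and febrile neutropenia. It also notes that hypogonadism may affect how patients' muscle adapts to resistance training.

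**The concern.** A common-variance test is safe when the two groups have similar variances, and nearly safe when they have similar sizes. Randomisation gives STR versus UNT reasonable cover on both counts. STR versus CON has no such cover: one group is men receiving cisplatin-based chemotherapy, the other is healthy volunteers chosen to match on age, BMI and training history.

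If medical dropout makes STR the smaller group, and toxicity, missed sessions or hypogonadism make its response more variable, the pooled error variance is weighted towards the larger, less variable group. The standard error is then too small and the test rejects too often. The result at risk is a false statement that chemotherapy changes the training response. An interval built on the same error term would be too narrow. If patients instead vary less than controls, the same mechanism makes the test conservative.

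**Working it through.** **Inputs from the article**

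- Test: ordinary group × time ANOVA at 0.05 (Analytic Plan). Two-sided is assumed, because sidedness is not stated.
- Planned sizes: 15 STR and 15 CON (Randomization).
- Minimum size: 10 per group. The stated formula reproduces: (1.28 × √(0.15 × 0.85))² / 0.15² = 9.28, rounded up to 10. Going from 15 to 10 is a loss of one third.

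**Inputs assumed, because the article does not give them**

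- The STR:CON ratio of SDs of change. The sample size formula contains only a binomial term, √(0.15 × 0.85), and no SD of fibre area. Range used: 0.67 to 2.
- Completers by arm. Range used: 10 to 15 STR, against 15 CON.

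**Step 1: how far the pooled standard error is off**

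Set the CON SD to 1 and the STR SD to r, with n₁ STR and n₂ CON completers.

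- True variance of the mean difference: r²/n₁ + 1/n₂
- Expected value used by the pooled test: [(n₁−1)r² + (n₂−1)] / (n₁+n₂−2) × (1/n₁ + 1/n₂)

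10 versus 15, r = 2:
- True: 4/10 + 1/15 = 0.467
- Pooled: (9×4 + 14)/23 × (1/10 + 1/15) = 2.174 × 0.1667 = 0.362
- Standard error ratio: √(0.362/0.467) = 0.88, about 12% too small

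10 versus 15, r = 0.67:
- True: 0.449/10 + 1/15 = 0.112
- Pooled: (9×0.449 + 14)/23 × 0.1667 = 0.131
- Standard error ratio: √(0.131/0.112) = 1.08, about 8% too large

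15 versus 15, r = 2: both expressions equal 0.333, so there is no bias in the standard error at equal sizes.

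**Step 2: type I error by simulation**

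Normal changes, no true group difference, 400,000 trials per cell, pooled t test on the change score. With two time points this is identical to the group × time F test.

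| STR vs CON completers | ratio 0.67 | ratio 1 | ratio 1.5 | ratio 2 |
|---|---|---|---|---|
| 10 vs 15 | 3.6% | 5.0% | 7.0% | 8.7% |
| 12 vs 15 | 4.3% | 5.0% | 6.1% | 7.1% |
| 15 vs 15 | 5.1% | 5.0% | 5.1% | 5.3% |
| 10 vs 10 | 5.1% | 5.0% | 5.2% | 5.5% |

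Repeat runs differ by about 0.1 percentage point. The Welch test stays between about 4.8% and 5.1% in all of these cells.

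**Step 3: all three assessments in the model**

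For the three-time-point group × time F test, assuming sphericity (100,000 trials per cell), ratios 1.5 and 2 give 7.6% and 9.9% at 10 versus 15, 6.7% and 7.5% at 12 versus 15, and 5.1% and 5.3% at 15 versus 15.

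**Step 4: price of the alternative**

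With equal variances and an illustrative true difference of 1.2 SD, power is about 80.3% (pooled) against 79.3% (Welch) at 10 versus 15, and 88.7% against 88.6% at 15 versus 15.

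**The case against.** The strongest reply is that the article shows neither ingredient. It gives no SD for any arm and nowhere says that patients respond more variably; the Discussion passage is about practical obstacles to training. A response blunted by hypogonadism might even vary less. The dropout allowance is made for every group, CON included, and CON has its own 21-week programme and the same biopsies, so losing a third of STR and none of CON is an extreme split. A null in which chemotherapy widens the spread of response but leaves its mean unchanged is also somewhat artificial, because the authors expect deterioration. Finally, the Analytic Plan is four sentences in a journal article, and variance handling is often left to a fuller plan.

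Most of this stands, and it rules out two stronger readings that a reader might infer. One is that the STR versus CON test runs at 7% to 9%: those figures belong to the 10-versus-15 split with ratios of 1.5 to 2, neither of which the article states. The other is that the error can only go towards false positives: that holds only if the smaller group also has the larger variance.

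The last argument does not remove the point. The article does more than stay silent on the method: it names an ANOVA for this comparison and sets out an exception only for mRNA and protein outcomes. A better choice can be recommended without assuming that anything is missing.

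**Conclusion.** The point holds as a conditional robustness remark. The stated method for STR versus CON assumes a common variance in a patient-versus-healthy comparison where the design guarantees neither equal spread nor equal completion. For SD ratios of 1 to 2 with 10 to 15 STR and 15 CON completers, the nominal 5% test on change scores runs at about 5% to 9%. It stays near 5% at equal sizes and drops to 3.6% at 10 versus 15 if the ratio is 0.67. With three time points the upper end is about 10%.

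These figures rest on the assumed SD ratio, on assumed differential dropout and on normally distributed changes. The randomised STR versus UNT comparison is much less exposed, because both arms are patients with the same diagnosis and chemotherapy. This is a cheap improvement; no figure stated in the article is wrong on this account.

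**What to change.** For every comparison with CON on an ANOVA-analysed outcome, pre-specify an analysis that lets the variance differ by group. Either of these would do:

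- a Welch test and confidence interval on the baseline-to-week-9 change; or
- the repeated-measures model with group-specific variances and Satterthwaite or Kenward-Roger degrees of freedom.

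Fix this in advance and do not make it depend on a preliminary test of variances, which has little power at 10 to 15 per group. Report completers and the SD of change by group, so that readers can see which part of the range applied.

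The cost is one clause in the analysis plan. If the variances turn out equal, the loss is a few degrees of freedom, a slightly wider interval and about one percentage point of power or less.

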## Abstract

**Background:**

Standard treatment for patients with disseminated germ cell tumors is combination chemotherapy with bleomycin, etoposide and cisplatin (BEP). This treatment is highly effective, but the majority of patients experience severe adverse effects during treatment and are at risk of developing considerable long-term morbidity, including second malignant neoplasms, cardiovascular disease, and pulmonary toxicity. One neglected side effect is the significant muscular fatigue mentioned by many patients with testicular cancer both during and after treatment. Very limited information exists concerning the patho-physiological effects of antineoplastic agents on skeletal muscle. The primary aim of this study is to investigate the effects of BEP-treatment on the skeletal musculature in testicular cancer patients, and to examine whether the expected treatment-induced muscular deterioration can be attenuated or even reversed by high intensity progressive resistance training (HIPRT).

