#### Healthy control subjects

15 healthy control subjects, matching TC patients in the following parameters: age, BMI and exercise training history, will be included in the study. This intervention-arm will represent the "standard" effect of HIPRT in young men not affected by antineoplastic treatment. The study will be conducted according to the CONSORT (Consolidated Standards of Reporting Trials) statement for non-pharmacological interventions[6], and has been approved by the Regional Ethics committee for the Capital Region (protocol nr: H-1-2010-049) and the Danish Data Protection Agency (jr.nr. 2010-41-5118).

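### The STR vs CON test of BEP's effect on the training response also contains BEP's own muscle loss, which biases it towards apparent blunting; relabel it and add a three-group contrast to week 9

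*Protocol article*

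**What the plan says.** The Analytic Plan (Methods/Design) names three sets of tests:

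- A one-way repeated-measures ANOVA in each group, which "will be used to evaluate test-data within groups for assessments at baseline, 9 and 21 weeks".
- A two-way group-by-time ANOVA of STR vs UNT.
- A two-way group-by-time ANOVA of STR vs CON.

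The two-way tests are to assess "the effect of HIPRT for TC patients (STR vs. UNT), and BEP-treatment for training response (STR vs. CON) respectively". On the error rate the plan says "Significance level of 0.05 is chosen". UNT enters only its own within-group analysis and STR vs UNT. No contrast uses all three groups.

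The section on healthy control subjects gives CON its role: "This intervention-arm will represent the 'standard' effect of HIPRT in young men not affected by antineoplastic treatment". Under Study arm 2, UNT has usual care during the nine weeks of chemotherapy and is offered the training programme only afterwards. The Abstract's Background states the premise about BEP: the study asks whether "the expected treatment-induced muscular deterioration can be attenuated or even reversed" by training.

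**The concern.** The three groups are three cells of a two-by-two layout (BEP yes/no, training yes/no). The cell with neither is missing. A question about whether BEP changes the response to training concerns an interaction. STR vs CON compares two trained groups, one with BEP and one without, so it measures everything BEP does to muscle during training. That includes any loss BEP would cause in a man who did not train. The plan attributes the whole difference to an effect on training response.

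This is separate from CON not being randomised: the direct BEP effect would remain in the contrast with a perfectly matched control group. At stake is the interpretation of one of the two planned between-group tests. The Discussion leaves open "whether TC patients undergoing chemotherapy experience attenuated exercise response because of treatment induced hypogonadism is currently unknown". STR vs CON cannot separate an attenuated response from ordinary muscle loss under chemotherapy.

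**Working it through.** **The plan's own figure.** Sample size: (1.28 × √(0.15 × 0.85))² / 0.15² = 9.28, rounded up to 10. It reproduces. It concerns hypertrophy "in CON, among whom a 15% increase is estimated according to earlier studies" and does not bear on STR vs CON.

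**Inputs**
- From the documents: T = 15 points (training effect in healthy men, Sample size section); 10 needed and 15 enrolled per group; alpha 0.05, taken as two-sided because sidedness is not stated.
- Assumed: direct BEP loss by week 9, L = 0, 5, 10 or 15 points; SD of a man's change 10, 15 or 20 points. The documents give neither.
- I = BEP's modification of the training response (0 means intact); g = nine-week change in untrained healthy men, which no group measures.

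**Expected change, baseline to week 9**
- CON = g + T
- UNT = g - L
- STR = g + T - L + I

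Hence:
- STR - CON = I - L
- STR - UNT = T + I
- (STR - UNT) - CON = I - g

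**Example** with I = 0, g = 0, T = 15, L = 10: CON +15, UNT -10, STR +5. STR - CON = -10, although training is worth 5 - (-10) = 15 points in patients, the same as in healthy men. The three-group contrast is 15 - 15 = 0.

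**How often STR vs CON would be significant when I = 0.** Two-sample noncentral t on change scores (equivalent to group by time with two time points), SE = SD × √(2/n), df = 2n - 2. For SD 15 and n = 15: SE = 15 × √(2/15) = 5.48, noncentrality 10/5.48 = 1.83, rejection 42%.

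| L (assumed) | n per arm | SD 10 | SD 15 | SD 20 |
|---|---|---|---|---|
| 0 | 15 | 5% | 5% | 5% |
| 5 | 15 | 26% | 14% | 10% |
| 10 | 15 | 75% | 42% | 26% |
| 15 | 15 | 98% | 75% | 51% |
| 10 | 10 | 56% | 29% | 19% |

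A simulation of 20,000 trials per setting at SD 15 agreed with these rates. In the same runs, which set g = 0, the three-group contrast rejected in about 5%.

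**Precision.** Var(STR - CON) = 2σ²/n and Var(STR - UNT - CON) = 3σ²/n, so the SE ratio is √(3/2) = 1.22. At SD 15 and n = 15 the SEs are 5.48 and 6.71. The 95% half-widths are 11.2 points (28 df) and 13.5 points (42 df).

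**Scale.** If the effects multiply (-10% and +15%), STR is 0.90 × 1.15 - 1 = +3.5%. The raw contrast is then (3.5 + 10) - 15 = -1.5 points with no modification at all. On the log scale it is 0.

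**The case against.** The strongest reply is that training response may simply mean the change observed while training. STR vs CON then compares that change with and without BEP, and CON is the benchmark trajectory the protocol describes. This stands in part: the comparison is legitimate and should be kept. It does not rescue the label, because the result would still be attributed to BEP's effect on training response with muscle loss mixed in.

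Three further points stand and limit the finding.

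- The primary aim does not rest on this contrast. What BEP does to muscle is addressed by UNT's within-group analysis, and whether training offsets it by the randomised STR vs UNT. Because both are planned, a reader would see UNT's change beside STR vs CON. But no estimate or interval for the combined question is specified, and comparing separate p-values does not supply one.
- The three-group contrast is not assumption-free. It equals I - g, so it is unbiased only if untrained healthy men would not change. In STR vs CON, time and retest effects common to both groups cancel. In the new contrast CON's share remains, and positive retest learning pushes it towards blunting. The Discussion says MVC and LEP were chosen to minimise familiarisation, which is not the same as removing it.
- CON is not randomised, so disease and testosterone differences remain in both contrasts.

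A reader might infer that an intact training response would necessarily be reported as blunted. The documents do not support that. The direction of bias follows from their expectation of deterioration, but significance depends on a loss and an SD they do not give, and they set no rule for wording the result.

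**Conclusion.** The point holds as a bias in one supporting, non-randomised comparison. STR vs CON has expectation I - L. Given the protocol's own expectation that L is above zero, it is shifted towards apparent blunting by the full size of the loss. The direction needs only L > 0; with L = 0 there is no bias.

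The size is illustrative. At 15 per arm, an assumed 10-point loss makes a false significant result about 5 to 15 times as frequent as the nominal 5% (26% to 75%, SD 20 to 10). A 5-point loss gives 10% to 26%.

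Two stronger conclusions are tempting and not supported. The trial's main conclusions are not at risk, because the UNT within-group and STR vs UNT analyses are unaffected. Nor is (STR - UNT) - CON simply the right answer: it replaces the implicit assumption L = 0, which the protocol itself does not hold, with the assumption g = 0, which is milder for fibre area and doubtful for strength and power tests. Grade: should be fixed.

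**What to change.** In the Analytic Plan:

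1. Keep STR vs CON, but describe it as the net difference in change under training, reflecting BEP and disease together and not randomised.
2. Add the contrast (STR - UNT) - CON from one model fitted to all three groups, with a 95% CI. Restrict it to baseline to week 9, because UNT is offered training afterwards and no longer isolates the BEP loss at week 21.
3. Use log fibre area for the fibre-area outcome, so that an equal percentage response counts as equal.
4. State the assumption that untrained healthy men do not change over nine weeks. Show the result over a range of such change, labelled as assumed because the documents provide none. Each point of change moves the contrast one point the other way.
5. For MVC and LEP, call the contrast exploratory, because retest learning in CON enters it in the direction of blunting.

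No new data are needed; the baseline and post-intervention assessments are already scheduled for all three groups. The cost is a standard error about 1.22 times that of STR vs CON (half-width 13.5 rather than 11.2 points at SD 15 and 15 per arm) and an assumption the trial cannot test.

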#### Study arm 1: HIPRT for TC patients during and after BEP treatment (STR)

This group will conduct a 9 week HIPRT-program, initiated at day 1 of the treatment, and will be offered a 12 week rehabilitation-program after the course of chemotherapy.

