#### Study arm 3: HIPRT for healthy matched control subjects (CON)

This group will conduct a 21 week HIPRT program following the same progression as STR.

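### STR vs CON is labelled a test of BEP's effect on training response, but it compares patients with non-randomised healthy men, so a difference cannot be credited to BEP alone

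*Protocol article*

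**What the plan says.** The Analytic Plan uses a 2-way ANOVA (group by time) for two between-group contrasts. STR vs UNT is to test the effect of HIPRT in patients. STR vs CON is to test the effect of "BEP-treatment for training response (STR vs. CON) respectively". The assessments are at baseline, 9 and 21 weeks, and "Significance level of 0.05 is chosen".

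The Randomization section randomises patients between STR and UNT only. For the third arm it says: "The healthy CONtrol subjects (CON, n = 15) will be allocated to HIPRT without randomization". The section on healthy control subjects gives three matching factors (age, BMI and exercise training history) and treats CON as showing the usual HIPRT effect in young men without antineoplastic treatment. The Recruitment section finds CON through newspaper and internet announcements.

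The Discussion states: "TC patients, however, may be affected by the presence of hypogonadism, which can significantly affect muscular adaptations to resistance exercise". It adds that up to half of Leydig cells are lost at unilateral orchiectomy. It also argues that the tumour probably matters little after the first cycle. Testosterone is not among the endpoints in Table 3 or the blood analyses described under Secondary outcome.

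After week 9, STR "will be offered a 12 week rehabilitation-program after the course of chemotherapy". For CON the text is: "This group will conduct a 21 week HIPRT program following the same progression as STR". The Abstract has CON complete the same programme as the 9-week one given to STR.

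**The concern.** The two contrasts get the same test and the same causal wording, but only one has randomisation behind it. In STR vs CON, every man given BEP has disseminated germ cell cancer and every man not given BEP is healthy. An ANOVA on these two groups cannot tell the effect of BEP on the training response from the effect of the disease, or from a hormonal deficit already present when BEP starts.

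At stake is what a significant STR-CON interaction would be taken to show. Followed as written, it would be reported as BEP blunting (or not blunting) adaptation to resistance training. The Discussion invites this reading by saying that the design permits study of the direct effects of antineoplastic therapy on muscle.

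**Working it through.** **1. What differs between STR and CON, by source**

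| Factor | STR | CON | Status in the contrast |
|---|---|---|---|
| BEP, including its hospital days and any hypogonadism it causes | yes | no | the exposure, its delivery and its pathway |
| Disseminated cancer | all | none | inseparable from BEP |
| Hypogonadism before BEP (orchiectomy-related) | possible | not expected | confounder; not measured in the listed analyses |
| Age, BMI, training history | matched | matched | addressed by design |
| Planned training to week 9 | HIPRT | HIPRT | the same |
| Training in weeks 9 to 21 | offered | to be conducted | uptake may differ |

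**2. Does group by time remove the problem?** The interaction compares changes from baseline, so a stable difference in level drops out. The factors at issue act on the change itself. Hypogonadism is said to alter adaptation to training. Patients are also tested at baseline before the first cycle, when the tumour is untreated, so their change includes any effect of tumour regression; the change in CON does not.

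**3. Training after week 9.** For STR, 9 + 12 = 21 weeks, the length given for CON. The Study arm 1 heading describes HIPRT both during and after BEP, and CON is to follow the same progression as STR. The planned content may therefore be identical. The visible difference is an offer against a requirement, and it affects only the 21-week assessment.

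**4. The plan's own figure.** The only calculation in the article is the sample size: (1.28 × √(0.15 × 0.85))² / 0.15² = 0.208896 / 0.0225 = 9.28. This agrees with the stated value, which is raised to 10 and then to 15 per group. It is based on hypertrophy within CON and says nothing about the STR-CON contrast or its confounding.

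**5. Illustration of consequence.** Assume that BEP has no effect, that non-BEP factors shift the mean change by d SD of the change, that the test is two-sided at 5% (the article does not state sidedness), and that a two-sample t-test is applied to the change. With two time points this t-test is equivalent to the group-by-time test. With n per group, the degrees of freedom are 2n − 2 and the noncentrality is d × √(n/2). For n = 15 this is 28 degrees of freedom and d × 2.739; for n = 10 it is 18 and d × 2.236. The rejection probability from the noncentral t distribution is:

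| Assumed d | n = 15 per group | n = 10 per group |
|---|---|---|
| 0 | 5% | 5% |
| 0.2 | 8% | 7% |
| 0.3 | 13% | 10% |
| 0.5 | 26% | 19% |
| 0.8 | 56% | 40% |
| 1.0 | 75% | 56% |

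No passage supports any particular d. The table shows only how a given amount of confounding would turn into findings credited to BEP.

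**The case against.** The article is open about the design. It says CON is not randomised, explains that testicular cancer was chosen because the tumour responds quickly, and says it is unknown whether treatment-induced hypogonadism weakens the exercise response. Matching covers three relevant factors, and the interaction already works on change. Covariate detail can reasonably sit in a fuller plan. All of this stands, and it limits the point to how the contrast is labelled and read. It does not rescue the label: the argument about tumour influence is asserted rather than measured, and the caution in the Discussion is not carried into the Analytic Plan.

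A reader might also infer several stronger things that the documents do not support:

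- *That STR and CON follow different programmes after week 9.* The Study arm 1 heading and the shared progression suggest the same content; only uptake may differ.
- *That hospital days and all hypogonadism are confounders.* The hospital days are part of giving BEP, and hypogonadism caused by BEP is a route by which BEP acts. Only the part that precedes treatment can confound, and the article does not say that every patient had an orchiectomy.
- *That the trial's main aim fails.* The effect of BEP on muscle can also be examined within groups, including UNT, who receive BEP without HIPRT during treatment. Whether HIPRT attenuates deterioration is tested by the randomised STR vs UNT comparison. STR vs CON bears on training response and leaves that comparison untouched.

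**Conclusion.** The point holds as one of attribution. STR vs CON can show whether BEP-treated testicular cancer patients respond to training differently from matched healthy men. It cannot show that BEP is the reason, because cancer and any pre-treatment hormonal deficit come with it. This follows from the design as stated and needs no numerical assumption.

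The size of the confounding is unknown. The 8%, 26% and 56% rejection rates belong to assumed shifts of 0.2, 0.5 and 0.8 SD at 15 per group; they are not estimates of this trial's error rate. The week-9 comparison is the cleaner one because planned training is the same up to then. The week-21 comparison carries a possible further difference in uptake, but it need not be dropped.

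**What to change.** - Reword the Analytic Plan so that STR vs CON is a non-randomised, exploratory comparison of training response in BEP-treated testicular cancer patients and matched healthy men. Remove the wording that credits the difference to BEP.
- Reserve confirmatory inference for the randomised STR vs UNT comparison.
- Take the main STR vs CON reading from baseline to week 9, and report week 21 descriptively.
- Reconcile the Abstract with the Study arm 1 and Study arm 3 descriptions of training after week 9.
- Optionally, assay testosterone in blood already scheduled. Use only the baseline, pre-BEP value as a covariate, in a sensitivity analysis. Report later values descriptively: adjusting for them could remove part of the BEP effect, since they may lie on its pathway.

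The wording changes cost almost nothing and need no new visits or procedures. The optional assay adds a small laboratory cost.
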